## Methods/design

### Study objectives

The primary objective of the Influence of Morphine on Pharmacokinetics and Pharmacodynamics of Ticagrelor in Patients with Acute Myocardial Infarction (IMPRESSION) study is to test the hypothesis that intravenous administration of morphine prior to ticagrelor administration in patients with AMI alters the plasma concentrations of ticagrelor and its active metabolite.

The secondary objective of this study is to determine whether intravenous administration of morphine prior to ticagrelor administration in AMI patients attenuates the antiplatelet effects of ticagrelor.

Additionally, a predefined subanalysis has been planned to investigate which of the platelet reactivity assessment methods utilized in the study best reflects concentration of ticagrelor and its active metabolite.

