### Study design and population

The IMPRESSION study is a phase IV, single center, randomized, double-blind, placebo-controlled, PK and PD clinical trial. The study population includes subjects presenting with AMI, including both STEMI and NSTEMI patients. After admission to the study center (Cardiology Clinic, Dr. A. Jurasz University Hospital, Bydgoszcz, Poland) and confirmation of the initial STEMI or NSTEMI diagnosis, patients will receive orally a 300-mg loading dose of plain aspirin and will be screened for eligibility for the study. The inclusion and exclusion criteria are as listed in Table 1. Eligible patients will be randomly assigned in a 1:1 ratio to one of two study arms. The patients in the intervention arm will receive 5 mg of morphine intravenously (IV) followed by a 180-mg loading dose of ticagrelor, whereas patients in the control arm will obtain 5 mg of a placebo IV followed by a 180-mg loading dose of ticagrelor (Figure 1). Subsequently all patients will undergo a coronary angiography followed by percutaneous coronary intervention (PCI), if necessary. Blood samples for PK and PD assessment will be drawn at eight predefined time points during the first 12 hours after randomization, according to the blood sampling schedule as presented in Figure 2. A telephone follow-up will be conducted at 30 days post-randomization, which will conclude the subject’s participation in the study.

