**Table 1 Tab1:** **Inclusion and exclusion criteria for IMPRESSION study**

Inclusion Criteria	
Provision of informed consent prior to any study-specific procedures	Provision of informed consent for angiography and PCI
Diagnosis of acute STEMI or acute NSTEMI	Male or non-pregnant female, aged 18 to 80 years old
Exclusion Criteria	
Chest pain described by the patient as unbearable or patient’s request for analgesics	History of major surgery or severe trauma (within 3 months)
Prior morphine administration during the current STEMI or NSTEMI	Patients considered by the investigator to be at risk of bradycardic events
Treatment with ticlopidine, clopidogrel, prasugrel, or ticagrelor within 14 days before the study enrollment	Second- or third-degree atrioventricular block during screening for eligibility
Hypersensitivity to ticagrelor	Patient required dialysis
Current treatment with oral anticoagulant or chronic therapy with LMWH	History of asthma or severe chronic obstructive pulmonary disease
Active bleeding	Manifest infection or inflammatory state
History of intracranial hemorrhage	Killip class III or IV during screening for eligibility
Recent gastrointestinal bleeding (within 30 days)	Respiratory failure
History of coagulation disorders	History of severe chronic heart failure (NYHA class III or IV)
Concomitant therapy with strong CYP3A inducers (rifampicin, phenytoin, carbamazepine, dexamethasone, phenobarbital) within 14 days and during study treatment	Concomitant therapy with strong CYP3A inhibitors (ketoconazole, itraconazole, voriconazole, telithromycin, clarithromycin, nefazadone, ritonavir, saquinavir, nelfinavir, indinavir, atazanavir)
Hemoglobin concentration less than 10.0 g/dl	Platelet count less than <100 x10^3/mcl
History of moderate or severe hepatic impairment	Body weight below 50 kg

LMWH: low-molecular-weight heparin; NSTEMI: non-ST-segment elevation myocardial infarction; NYHA: New York Heart Association; PCI: percutaneous coronary intervention; STEMI: ST-segment elevation myocardial infarction.

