### Pharmacodynamics

Assessment of ticagrelor’s antiplatelet effects will be performed using up to four different methods (Figure 3). A platelet vasodilator-stimulated phosphoprotein (VASP) assay will be applied to all study participants at all predefined time points (Figure 2). Multiple electrode aggregometry (MEA) will be used at all predefined time points for all study participants with the exception of those treated with glycoprotein IIb/IIIa (GP IIb/IIIa) receptor inhibitors. VerifyNow and light transmission aggregometry (LTA) will be applied for at least 30% of all enrolled study participants at all predefined time points. Measurements with VerifyNow and LTA will not be performed in patients treated with GP IIb/IIIa receptor inhibitors. Details regarding methods to be used for the assessment of platelet reactivity were previously described [11-14].

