### Study endpoints

The primary endpoint of this trial is the area under the plasma concentration-time curve (AUC_(0–12)_) for ticagrelor for the first 12 hours after the loading dose of ticagrelor. Secondary endpoints include AUC_(0–12)_ for AR-C124910XX, maximum concentration (Cmax) of ticagrelor and AR-C124910XX, time to Cmax for ticagrelor and AR-C124910XX, platelet reactivity index (PRI) assessed by VASP assay, area under the aggregation curve assessed by MEA, P2Y12 reaction units (PRU) assessed by VerifyNow, and ADP-induced platelet aggregation assessed by LTA.

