### Statistics

Since there is no reference study examining the PK of ticagrelor in patients presenting with STEMI or NSTEMI, we decided to perform an internal pilot study of approximately 30 patients (15 patients for each arm) to estimate the final sample size. The means and standard deviations of AUC_(0–12)_ for ticagrelor in the first 33 patients assessed for patients who received morphine and for patients who received the placebo were 6,917 ± 4,920 and 10,379 ± 5,996 ng · h/ml, respectively. Based on these results and assuming a two-sided alpha value of 0.05, we calculated, using the *t*-test for independent variables, that enrollment of 68 patients would provide an 80% power to demonstrate a significant difference in AUC_(0–12)_ for ticagrelor between patients who received morphine prior to a loading dose of ticagrelor and those who received the placebo prior to the ticagrelor loading dose.

Continuous variables will be compared between both study arms by the Student’s *t*-test or the Mann–Whitney *U* test, depending on the presence or absence of the normal distribution (as assessed by the Kolmogorov-Smirnov test). Proportions will be compared by the Fisher exact test or chi-square test when appropriate. Pharmacokinetic calculations will be performed using a dedicated software.

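### The platelet endpoints are tested without adjustment for each patient's pre-dose reactivity: valid, but inefficient if the schedule contains a draw before the study-drug injection

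*Protocol article*

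**What the plan says.** The Statistics section states that "Continuous variables will be compared between both study arms by the" Student's t-test or the Mann–Whitney U test, with a Kolmogorov–Smirnov check deciding between them. It makes no exception for the platelet measures and names no covariate.

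Study endpoints lists the platelet measures by assay and unit: "platelet reactivity index (PRI) assessed by VASP assay, area under the aggregation curve assessed by MEA, P2Y12 reaction units (PRU) assessed by VerifyNow", and ADP-induced aggregation by LTA. It gives no time point, change from baseline or adjustment.

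Study objectives asks whether morphine "attenuates the antiplatelet effects of ticagrelor".

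On data collection, Study design and population says: "Blood samples for PK and PD assessment will be drawn at eight predefined time points during the first 12 hours after randomization". The study-drug injection (morphine or placebo) comes before ticagrelor. Pharmacodynamics says the VASP "assay will be applied to all study participants at all predefined time points". MEA is also run at all times, except in patients given GP IIb/IIIa inhibitors. VerifyNow and LTA cover at least 30% of patients. Table 1 excludes "Treatment with ticlopidine, clopidogrel, prasugrel, or ticagrelor within 14 days before the study enrollment".

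**The concern.** Platelet reactivity differs between patients before any P2Y12 blocker is given. A post-dose level therefore carries both the drug's effect and the patient's starting point. A two-sample test leaves the starting-point variation in its standard error. If a pre-treatment value of the same assay has been measured, an analysis that uses it estimates the same arm difference more precisely, at almost no cost.

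This matters because the platelet endpoints carry the whole secondary objective, the trial is small, and no power is stated for any of them. VerifyNow and LTA may be available in only about 20 patients (30% of 68 = 20.4). The primary endpoint, ticagrelor AUC, has no baseline value to adjust for, so the point does not reach it.

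**Working it through.** **Is the unadjusted test fixed by the document?** Yes. The Statistics rule applies to all continuous variables, and nothing in Study endpoints modifies it for the platelet assays.

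**Is there a pre-dose value to use?** Sampling is counted from randomization, both drugs follow randomization, and recent P2Y12 blocker users are excluded. A first draw giving untreated P2Y12 reactivity is therefore plausible. No text states it, because the schedule is in Figure 2, which is not shown. A usable covariate must precede the injection and not only ticagrelor, since morphine is given first.

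**Illustrative effect size.** The only effect size in the document is from the AUC pilot in Statistics: 6,917 (SD 4,920) against 10,379 (SD 5,996).
- Difference = 10,379 − 6,917 = 3,462.
- SD = √((4,920² + 5,996²)/2) = 5,484.5.
- Effect = 3,462 / 5,484.5 = 0.631 SD.

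**The plan's own figure.** From these inputs, 80% power at two-sided 0.05 needs 80 patients in total (normal approximation) or 82 (t-test), not the stated 68. With 34 per arm the t-test has 73% power. That mismatch concerns the AUC and is a separate matter. It is noted here only because it explains why the comparison below starts at 73% and not 80%.

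**Power with and without the covariate, 34 per arm.** Let r be the correlation between pre-injection and post-dose values (assumed; not in the document). The covariate reduces the residual SD by the factor √(1 − r²). Power comes from the noncentral t distribution with noncentrality (0.631/√(1 − r²)) × √(34/2), on 65 degrees of freedom instead of 66. Simulation (6,000 runs per cell, normal data) agrees.

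| r | √(1 − r²) | Noncentrality | Power, noncentral t | Power, simulated |
|---|---|---|---|---|
| unadjusted t-test | 1 | 2.60 | 73% | 72–73% |
| 0 | 1 | 2.60 | 73% | 72% |
| 0.3 | 0.954 | 2.73 | 77% | 76% |
| 0.5 | 0.866 | 3.01 | 84% | 84% |
| 0.7 | 0.714 | 3.64 | 95% | 95% |

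The formula is slightly optimistic because it ignores the small precision cost of chance covariate imbalance; the simulation includes it. The unadjusted Mann–Whitney test gives 70% to 71% on the same data.

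**The same gain in patients.** The adjusted analysis matches the precision of 68 unadjusted patients with 68 × (1 − r²) patients: 61.9, 51.0 and 34.7 at r = 0.3, 0.5 and 0.7.

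**The smallest subset.** At 10 per arm, simulated power is about 26% unadjusted, and 26%, 31% and 44% adjusted at the same three values of r.

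**Is the unadjusted test invalid?** No. In 40,000 simulated null trials at 34 per arm its type I error was 5.0%, 5.0% and 5.1% at r = 0.3, 0.5 and 0.7. The error conditional on the observed starting imbalance varies in both directions:

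| Starting imbalance | r = 0.3 | r = 0.5 | r = 0.7 |
|---|---|---|---|
| under 1 SE | 4.3% | 3.2% | 1.6% |
| beyond 1.96 SE | 10% | 19% | 33% |

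One SE is √(2/34) = 0.243 SD. An imbalance above 0.5 SD (0.5/0.243 = 2.06 SE) has probability of about 4%.

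**Why not a change score?** Its SD is √(2(1 − r)) times the SD of the level, which is larger than 1 when r < 0.5. For an effect that the unadjusted test detects with 80% power at N = 68 (0.69 SD), a change score has 66% power at r = 0.3, against 84% for analysis of covariance.

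**The case against.** **No pre-dose draw is in evidence.** This stands as a limit. One cannot say that the information has been collected and discarded. The recommendation has to be conditional on the schedule, and specifically on a draw before the injection.

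**The article is condensed, and an unseen analysis plan may adjust.** This stands in part. Detail about time points and derived variables is rightly left to such a plan. The article does, however, state a test for all continuous variables, so an adjusted main analysis would depart from a published rule.

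**Comparing on-treatment reactivity between randomized arms already answers the secondary objective.** Correct. A reader might infer that chance starting differences will pass for a morphine effect and that the comparison is biased. The documents do not support that. Allocation is randomized and the overall error rate is 5%. The raised conditional rates belong to uncommon imbalances and are offset by rates below 5% when the arms start close together.

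**The size rests on borrowed numbers.** Also correct. The 0.63 SD comes from AUC and not from any platelet assay, and r is assumed. At r = 0.3 the gain is about 3 points at N = 68 and nil at 10 per arm.

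**The calculations use normal data, whereas the plan provides a rank test for non-normal data.** Fair. The remedy must include a transformed or rank-based version.

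**Conclusion.** The point holds as one of efficiency. The stated analysis of the platelet endpoints is valid, but it would leave precision unused if a pre-injection sample exists. For an illustrative 0.63 SD effect at 34 per arm, the gain is about 3, 11 or 22 percentage points of power (73% to 76%, 84% or 95%) at r = 0.3, 0.5 or 0.7, against a loss of under 1 point at r = 0.

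This rests on three assumptions that the document does not settle: that a pre-injection draw is scheduled, the value of r, and the size of the platelet effect. It concerns secondary endpoints only; the primary AUC comparison is untouched. The change is worth making because it costs little and can hardly do harm, not because the planned test would mislead.

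**What to change.** First confirm from the sampling schedule whether a draw precedes the study-drug injection. If it does, amend Statistics for PRI, MEA, VerifyNow and LTA before unblinded platelet data are analysed:

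- Main analysis: analysis of covariance, or a repeated-measures model, with arm as factor and the patient's own pre-injection value of the same assay as covariate.
- Use transformed or ranked values if the residuals are clearly non-normal.
- Report the adjusted arm difference with its 95% confidence interval.
- Keep the unadjusted t-test or Mann–Whitney test as a sensitivity analysis.
- Do not use a value drawn after the injection as the covariate, since morphine could already have influenced it. Do not substitute a change score.

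The cost is a change of wording, one degree of freedom per model, and a simple stated rule for patients with no pre-injection value. No extra patient, draw or assay is needed if the sample is already scheduled. If it is not, the unadjusted test can stand.

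### The primary ticagrelor AUC(0–12) is compared without adjustment for body weight, although the dose is fixed and weight must be known at screening; adjusting would be a near-costless gain in efficiency, of uncertain size

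*Protocol article*

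**What the plan says.** - **Endpoint.** Study endpoints defines the primary endpoint as the area under the concentration curve "for ticagrelor for the first 12 hours after the loading dose of ticagrelor".
- **Dose.** Study design and population gives both arms an intravenous injection (morphine or placebo) "followed by a 180-mg loading dose of ticagrelor". The dose is not scaled to body size.
- **Weight.** Table 1 lists "Body weight below 50 kg" as an exclusion and sets no upper limit. Table 2 tabulates BMI, but gives neither weight nor any measure of spread.
- **Analysis.** Statistics states: "Continuous variables will be compared between both study arms by the" Student t-test or the Mann–Whitney U test, chosen by a normality test. No covariate or adjusted model is named.
- **Sample size.** The same section uses pilot AUC values of "6,917 ± 4,920 and 10,379 ± 5,996" ng·h/ml (morphine, placebo), "assuming a two-sided alpha value of 0.05" and a "test for independent variables", and concludes that "enrollment of 68 patients would provide an 80% power".

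**The concern.** After a fixed oral dose, body size is a natural candidate predictor of exposure, because clearance and volume generally rise with size. That is general pharmacokinetic reasoning; the article gives no relation between weight and ticagrelor AUC. Weight is also a true baseline variable, cannot be affected by morphine, and has to be known to apply the eligibility criteria.

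The AUC is very variable: the SDs are 71% and 58% of the means (4,920/6,917 and 5,996/10,379). In an unadjusted comparison, any part of that variation due to weight stays in the error term. If weight does predict AUC, the trial forgoes some precision that it could have for almost nothing. Infarct type is a different source of variation, so adjusting for STEMI versus NSTEMI would not replace weight.

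**Working it through.** **Inputs from the Statistics section.** Means 6,917 and 10,379; SDs 4,920 and 5,996; two-sided alpha 0.05; 68 patients (34 per arm). The Abstract plans up to 100 patients, so 50 per arm is shown as well. The pilot values are taken as the truth, as the article does.

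**The plan's own figure.**
- Difference = 10,379 − 6,917 = 3,462.
- SD = √((4,920² + 5,996²)/2) = 5,484.
- Standardised difference d = 3,462/5,484 = 0.631.
- At 34 per arm, noncentrality = 0.631 × √(34/2) = 2.60 on 66 df, so the power is 72.7% (noncentral t; 74.0% by the normal approximation).
- 80% power needs 82 patients in total (80 by the normal approximation). The stated 68 does not reproduce. That is a separate issue; the baseline used here is the recomputed 72.7%.

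**How much of the variance might weight explain? (Assumptions.)** Suppose AUC varies inversely with clearance, clearance scales with weight to the power b = 0.75 to 1, and weight has a CV of 15% to 22%.
- SD of log AUC = √ln(1 + CV²): 0.640 (morphine), 0.537 (placebo).
- R² = (b × CV of weight / SD of log AUC)².
- Lowest: (0.75 × 0.15/0.640)² = 0.03. Highest: (1 × 0.22/0.537)² = 0.17.
- Because none of these inputs is in the article, R² = 0 is included in the range.

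**Raw scale.** The adjusted analysis has d/√(1 − R²) and loses one df.

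| R² (assumed) | Power, 34 per arm | Power, 50 per arm | Total N for 80% |
|---|---|---|---|
| unadjusted | 72.73% | 87.8% | 82 |
| 0 | 72.71% | 87.8% | – |
| 0.03 | 74.0% | 88.7% | 80 |
| 0.05 | 74.9% | 89.4% | 78 |
| 0.10 | 77.1% | 90.9% | 74 |
| 0.15 | 79.4% | 92.4% | 70 |
| 0.17 | 80.4% | 92.9% | 68 |

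**Log scale, assuming log-normal AUC.**
- Common log SD = √((0.640² + 0.537²)/2) = 0.591.
- Difference in log means = [ln 10,379 − 0.537²/2] − [ln 6,917 − 0.640²/2] = 0.467.
- d = 0.467/0.591 = 0.79.
- Power at 34 per arm: 89.4% unadjusted; 90.3% at R² 0.03, 90.9% at 0.05, 92.3% at 0.10 and 94.1% at 0.17.

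So weight adds about 1 to 5 points over R² 0.03 to 0.17. The step from 72.7% to 89.4% comes from the log transform under log-normality, not from the covariate.

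**Chance imbalance.** With an assumed weight SD of 15 kg, the SE of the difference in mean weight is 15 × √(2/34) = 3.64 kg. A difference above 5 kg between arms then occurs about 17% of the time. With that SD and the CVs above, mean weight lies between 15/0.22 = 68 kg and 15/0.15 = 100 kg, and a 5 kg difference moves AUC by about 4% to 7%. The pilot difference is 1 − 6,917/10,379 = 33%.

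**The case against.** The strongest reply is that nothing here is wrong. Under 1:1 randomisation the unadjusted comparison is unbiased and keeps its error rate. That stands, and it limits the point to efficiency.

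It can also be said that the quoted sentence is a general rule for continuous variables, and that covariates are often left to an analysis plan, which is not shown. Such a plan could add an adjusted analysis. But the article names the test and sizes the primary endpoint on it, so the choice is a stated one and can fairly be commented on.

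The weight–AUC relation is not in the article. Moreover, the R² derivation treats AUC as inverse to clearance, which suits complete exposure better than an area cut off at 12 hours after an oral dose in a trial about absorption. That stands: the upper end of the range has no support in the article, and zero cannot be excluded.

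Three stronger readings are tempting, and the article does not support them:
- **That precision is certainly being lost.** This is conditional on a correlation that is not reported.
- **That chance imbalance in weight undermines the unadjusted result.** Such imbalance is already reflected in its standard error and alpha, and the shift worked out above is small beside the pilot difference.
- **That weight is measured at screening.** Table 1 shows only that it must be known; how it is obtained is not stated.

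**Conclusion.** The point holds as a recommended improvement, not as an error. The stated primary comparison leaves out a baseline variable that must be available for every patient and that plausibly relates to exposure after a fixed dose.

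For an assumed R² of 0 to 0.17, the raw-scale gain is from nothing to about 8 percentage points at 34 per arm (72.7% to at most 80.4%) and at most about 5 points at 50 per arm (87.8% to 92.9%). On the log scale, which is the scale of the proposed model, the gain at 34 per arm is at most about 5 points (89% to 94%), if AUC is log-normal. All of these take the pilot means and SDs as true.

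The case for acting is the asymmetry: if weight explains nothing, raw-scale power at 34 per arm falls by only 0.02 points. A reader might infer that weight adjustment repairs the gap between 68 patients and the claimed 80% power. On the raw scale it would do so only at an R² of about 0.16 or more, so that shortfall must be dealt with separately.

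**What to change.** Prespecify the primary analysis as a linear model of log AUC(0–12) on treatment arm, with log body weight at screening as covariate. Report the adjusted ratio of geometric means with its 95% CI. Keep the unadjusted two-sample comparison as a sensitivity analysis. State how weight is obtained (measured or reported), and fix the model before the final unblinded analysis.

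**Cost.** A line or two of analysis text, one degree of freedom, and no added patients or data beyond a weight that eligibility already requires. The one substantive change is that the effect becomes a ratio of geometric means instead of a difference in means; the sample-size statement should be put on the same scale.

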## Discussion

The IMPRESSION study is a phase IV, single center, randomized, double-blind, placebo-controlled clinical trial that assesses the influence of morphine on the PK and antiplatelet effects of ticagrelor in patients with myocardial infarction. This trial will provide important information regarding the impact of morphine, the analgesic which is most commonly used in patients with AMI, on the absorption of ticagrelor in subjects presenting with STEMI and NSTEMI. Furthermore, the study could specify the suspected connection between alterations in ticagrelor absorption and modification of its antiplatelet activity. A disclosure of such drug-drug interaction in AMI patients could supply a significant evidence-based data source regarding concurrent use of ticagrelor and morphine in STEMI and NSTEMI treatment.

